**Methods:**

This study will use a nonrandomized controlled trial design with a qualitative evaluation to assess feasibility and acceptability. Data will be collected through student surveys, student focus groups, and teacher reflection journals. Two schools in New South Wales, Australia, will participate by implementing the TPSR framework in their programs. Schools will include classes in stages 3 and 4 of the intervention, involving approximately 90 students from each school. Both schools are located in Sydney, New South Wales: one is a government high school, and the other is an independent K-12 school. To address feasibility and accessibility concerns, the intervention will be delivered during regularly scheduled PE classes. It will be facilitated by students’ regular PE teachers, who will also participate in ongoing professional development and be involved in a co-design process with the research team. Primary outcomes include reporting on personal responsibility, social responsibility, and leadership behaviors, measured using two tools: (1) the Tool for Assessing Responsibility-Based Education and (2) the Personal and Social Responsibility Questionnaire. A secondary outcome, enjoyment, will be assessed using the Physical Activity Enjoyment Scale–Physical Education version. Feasibility and accessibility will also be examined as secondary outcomes.

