**Term 2**		
	8	Preintervention testing PSRQ^a^ and PACES-PE^b^ surveys administered
	9	Back-up dates for surveys
	10	—^c^

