**Term 3**		
	1 (athletics)	Zoom check-in (occurs every week) “Every name, every day” Class Goal HERO concept “Me time” “Good Game” at the conclusion of the lesson “Coaches and Players” in 3-week intervals
	2 (athletics)	TARE^d^ analysis
	3 (athletics)	—
	4 (athletics)	—
	5 (athletics)	TARE analysis
	6	—
	7	—
	8	TARE analysis
	9	—
	10	Postintervention testing PSRQ and PACES-PE surveys administered Focus groups completed

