### Participants

The participants in this study will be students from years 5, 6, and 8. Each intervention group in the study will need to have 77 students and a matched control group of the same size to detect 2-tailed statistical significance (*P*<.05) with 80% power (1−β=0.8). Two schools in the western suburbs of Sydney have been recruited to participate in the study: one is a government high school, and the other is an independent K-12 school. They have been chosen through professional networks who expressed interest in the TPSR study. Students in NSW generally participate in 1 PE lesson per week, which is where the intervention will take place. PE lessons in NSW high schools are delivered to students from years 7 to 10 and focus on skills development, alongside one or two sport lessons focused on game play.

Consent will be obtained from parents, students, and the school principals in line with the ethics requirements of the University of Sydney. Participants’ personal information and school names will be deidentified in all publications arising from the study. Students and teachers will also be briefed on the intervention before study commencement and given the opportunity to ask questions. Participants will be allowed to withdraw from the intervention at any time. All data collected, including data from focus interviews, surveys, meeting minutes, and consent forms, will be stored securely and encrypted with a password. If parents request details of intervention results, a lay summary will be provided.

Fidelity and acceptability will be addressed through teacher expertise and training, intervention location, timetabling, and time spent on the intervention. Teachers will participate in a professional development program before starting the intervention. The purpose of this program is to familiarize teachers with the TPSR framework and to facilitate the co-design of strategies and activities to integrate the framework into programs. This approach also means that students do not have to build relationships with or adapt to outside facilitators. Furthermore, it does not incur additional funding for the school or research team. The professional development program will comprise a 3-hour, face-to-face learning block before the intervention and ongoing check-ins with teachers using Zoom (Zoom Video Communications, Inc) for the duration of the intervention.

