### Intervention Design

This intervention will focus on providing opportunities for students to develop social skills in PE classes. Teachers will act as facilitators, and researchers will codevelop and adapt the intervention programs with them using a co-design process. A teacher professional development program will be administered before intervention commencement to ensure that teachers are familiar with the TPSR framework. Students will take part in focus groups before and after the intervention and will complete surveys measuring social outcomes. The researchers will be available for communication with teachers to maintain intervention integrity and to ensure that issues are addressed efficiently. Teachers will run their PE lessons with the TPSR framework embedded within their existing programs, minimizing additional workload. Examples of TPSR strategies that may be featured within lessons are provided in Table 1.

Before intervention commencement, students and teachers from the participating schools will complete preintervention testing, which will include surveys. Students at each school will then take part in the 10-week intervention and complete a postintervention test similar to the preintervention test. Focus groups will also be conducted during the posttest period. There will be a follow-up 5 weeks after the intervention. In line with the mandated requirements of the schools, students will participate in 1 PE lesson per week, which is standard practice in NSW schools. The duration of each lesson will depend on the school, with 45 to 60 minutes being typical in NSW schools. Social outcomes (personal responsibility and social responsibility) will be the primary focus of the intervention, as per the measurement tool.

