#### Quantitative Analysis

Quantitative data from the PSRQ, PACES-PE, and TPSR will be analyzed using SPSS software (version 30.0; IBM Corp). Internal consistency of the scales will be assessed using Cronbach α. The PSRQ will assess students’ self-perceived levels of personal and social responsibility, and the PACES-PE will assess enjoyment in PE. ANOVA will be conducted to compare mean scores before and after the intervention for both questionnaires. TARE data will be collected through lesson observations by the research team 3 times during the 10-week intervention period, and interrater reliability will be assessed using Cohen κ. Frequencies and mean scores of the TPSR strategies will be examined descriptively and across time to explore implementation fidelity. A repeated measures multivariate ANOVA will be performed to provide a more complex analysis of the findings and a more comprehensive view of how the intervention affects multiple variables simultaneously.

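### The named repeated measures MANOVA by default discards students with any incomplete post-baseline record; the power cost is small, but it leaves the comparison open to bias that a mixed model on all available data would reduce

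*Protocol article*

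**What the plan says.** The protocol article, Quantitative Analysis, first plans an ANOVA comparing mean questionnaire scores before and after the intervention. It then adds: "A repeated measures multivariate ANOVA will be performed", to look at several variables together. The software is SPSS 30.

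On sample size, Participants states: "Each intervention group in the study will need to have 77 students and a matched control group of the same size", for "2-tailed statistical significance" at P<.05 with 80% power. It gives no effect size, SD or expected loss. The Abstract (Methods) describes the planned enrolment as "involving approximately 90 students from each school", at two schools.

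On when data are collected:
- Table 2 puts the PSRQ and PACES-PE pretest in Term 2 week 8, and lists "Back-up dates for surveys" for week 9.
- For Term 3 week 10 it lists "Postintervention testing PSRQ and PACES-PE surveys administered", with focus groups in the same week and no back-up date.
- Intervention Design adds: "There will be a follow-up 5 weeks after the intervention". Neither that section nor Table 2 names the instruments used then.
- Measurement Tools places the PSRQ at pretest and posttest only.
- Eligibility Criteria require a completed pretest.

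On withdrawal, Participants says: "Participants will be allowed to withdraw from the intervention at any time".

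**The concern.** A repeated measures MANOVA in a standard general linear model routine needs one complete row per student: every dependent variable at every occasion entered. With no other step taken, the software removes a student with one blank cell. A missing PACES-PE form then also removes that student's PSRQ scores, and a missing posttest removes the pretest that was collected.

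Because the pretest is an entry condition, whole-questionnaire loss falls on the later waves. The posttest is the wave that carries the comparison. It sits in the last week of a 10-week term and lacks the spare week that the pretest has.

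Two things could be at stake: power, if the complete-case sample falls below the stated requirement, and bias, if the students who drop out of the model differ from those who stay and do so differently by arm. The arms are not randomised, so differential loss would add to any imbalance already present.

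**Working it through.** **Inputs.** 77 per group, two-sided 0.05 and 80% power (Participants). About 90 students at each of two schools (Abstract), taken here to cover both arms, so 2 × 90 = 180. One post-baseline PSRQ wave is documented (Measurement Tools, Table 2); a second is possible if the follow-up is analysed. Loss rates appear nowhere in the article and are assumed below. Clustering by class is ignored throughout.

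**The plan's own figure.** With no effect size stated, 77 cannot be reproduced forwards. Solved backwards with the normal approximation, d = √(2/77) × (1.960 + 0.842) = 0.452; the two-sample t-test gives 0.454. The required total is 77 + 77 = 154, a derived figure that is not printed.

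**Margin.** 1 − 154/180 = 14.4% total loss. Over two post-baseline waves with independent loss, 1 − √(154/180) = 7.5% per wave.

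**Complete cases and power.** N = 180 × (1 − loss)^waves, half per arm, at d = 0.454:

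| Assumed loss per wave | Posttest only: N (power) | Posttest and follow-up: N (power) |
|---|---|---|
| 10% | 180 × 0.90 = 162 (82%) | 180 × 0.90² = 146 (78%) |
| 15% | 180 × 0.85 = 153 (80%) | 180 × 0.85² = 130 (73%) |
| 20% | 180 × 0.80 = 144 (77%) | 180 × 0.80² = 115 (68%) |

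**Scale-level gaps.** If each of the two scales at posttest were blank for an independent 5% of students, 180 × 0.95² = 162 would remain. Both scales are given at the same session, so gaps would tend to coincide and the true loss would be smaller.

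**What a mixed model recovers.** With pretest and posttest only, a student without a posttest adds little precision to the arm-by-time contrast under any method, so the 82-80% figures would barely move. If the follow-up is analysed, 10% independent loss per wave leaves 180 × (1 − 0.10²) = 178 students with at least one later score, against 146 complete on both.

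**Bias.** Standardise the scores, let ρ be the pre-post correlation, and let loss depend on the baseline score only. Expected change given baseline Y₀ is then (ρ − 1)Y₀ plus the arm's mean change. If completers' mean baseline is shifted by δ in each arm, the complete-case arm-by-time estimate is off by (ρ − 1)(δ_intervention − δ_control).

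As an illustration, assume that one arm loses 15% of students whose baseline averages 0.6 SD below that arm's mean, while loss in the other arm is unrelated to baseline. Then δ = 0.15 × 0.6/0.85 = 0.106. With ρ = 0.5 the bias is 0.5 × 0.106 = 0.05 SD; for ρ from 0.4 to 0.7 it runs from 0.06 to 0.03 SD. Against d = 0.454, 0.05 SD is about 12%. The sign depends on which arm loses them. If both arms lose the same kind of student at the same rate, δ_intervention = δ_control and the bias is zero. A correctly specified likelihood model that keeps the lost students' pretests removes this component.

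**The case against.** The strongest reply is that this is a missing-data question in another form. The article never says that incomplete students are dropped. Listwise deletion is a software default, and imputation before the MANOVA would be compatible with the text and could sit in an analysis plan that is not shown. That stands in part: the absence of a missing-data rule from this article is no finding. The point here is narrower. The article does name a method, that method handles partial records poorly unless something is added, and a better one is available at almost no cost.

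The MANOVA is also an addition beside a pre-post ANOVA, and nothing ties the 77 to it. That is correct. However, a within-student pre-post ANOVA needs both scores too, so it does not retain a student who misses the posttest.

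A reader might infer several stronger things that the documents do not support:
- *That the sample will fall below what is needed.* On the documented schedule this takes more than 14.4% loss, and 15% leaves 153, one short of 154. The 146, 130 and 115 figures require the follow-up to enter the model, which the article does not state.
- *That any missing wave removes a student.* The pretest cannot be missing for an eligible student.
- *That the power losses are established.* The effect size is back-solved. A requirement of 64 per group at d = 0.50, multiplied by 1.2, also gives 77, so an attrition allowance may already be included. In that case 128 analysed would suffice and even 130 would meet it. Conversely, the sample-size sentence could mean 77 plus 77 at each school (308 in all), which 180 would miss with no loss at all.
- *That the analysed sample will be tilted towards engaged students.* Nothing in the documents shows who would be lost. The withdrawal sentence concerns the intervention, not survey absence.

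Finally, Table 2 is a summary, and an unlisted catch-up session is not ruled out.

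**Conclusion.** The concern holds in limited form. The named MANOVA, run with its default handling, uses only students complete on everything entered, and the posttest lacks the back-up date that the pretest has. The effect on power is minor on the documented two-wave schedule: 82-80% at 10-15% assumed loss. It becomes material (78-73%) only if the follow-up is analysed in the same model with that loss at each wave.

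The better reason to change is possible bias, of the order of 0.05 SD under the illustrative loss pattern above and zero if loss is alike in both arms. It is a plausible risk and not a demonstrated one. These sizes rest on assumed loss rates, an assumed pre-post correlation, a back-solved effect size, 180 covering both arms, and no allowance for clustering. A mixed model protects only where loss depends on observed scores; it does not cure loss that depends on the unseen posttest score.

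**What to change.** For each PSRQ subscale, make the main analysis a linear mixed model on all available measurements, with arm, time, arm-by-time, school and year as fixed effects and random effects for student and class. Keep the repeated measures MANOVA as a complete-case sensitivity analysis. State whether the 5-week follow-up enters the model and with which instruments. In Table 2, list a catch-up date for the posttest survey, as is done for the pretest, if the calendar still allows it.

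SPSS fits these models, so the cost is a change of wording before outcome data are examined, slightly more analysis work, and one catch-up survey slot.

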#### Qualitative Analysis

Focus group data will be collected from students to capture their experiences and perceptions of the TPSR program. Interviews will be analyzed using NVivo 15 (Lumivero) and the thematic analysis process developed by Clarke and Braun [34]. Representative quotes will be selected to exemplify key themes and bring student voice into the interpretation of the intervention’s impact [35].

### Fidelity

Fidelity measures are important in intervention studies because they reflect whether the intervention was implemented as intended [36]. Fidelity is also important when considering study replication and future work in related fields [36]. Ginsburg et al [36] argue that 3 common elements (ie, delivery, receipt, and enactment) are important in all fidelity models. This study aims to ensure that fidelity requirements are met through measures such as the professional development program for teachers, ensuring that they not only know and understand the TPSR framework but also know how to apply it in the intervention. This marks the co-design process as significant because researchers and teachers will work together to integrate TPSR elements into already existing PE programs. Fidelity measures will be gathered through both qualitative and quantitative methods, with students and teachers participating in focus groups before and after the intervention. Teachers will also complete a reflection journal at the conclusion of each lesson to assess the framework’s impact. This reflection journal will take <5 minutes to complete and will include the following questions:

“How would you rate student engagement with the responsibility themes today?” (1=not at all, 5=very highly)“Did you observe any signs of student progress in any of the themes? Comment with dot points below”“What was the most successful part of the lesson? Comment with dot points below”“Any changes for next time?”

A member of the research team will conduct check-ins using Microsoft Teams or Zoom at the conclusion of weeks 1, 3, 5, 7, and 9 to ensure that teachers’ questions are answered and implement contingencies if needed or when responses to question 4 in the teacher reflection journal indicate that changes are warranted.

## Results

Recruitment for the study concluded in December 2024. Participation in the 10-week TPSR intervention will commenced in term 3 of the 2025 school year. Ethics approval was obtained in 2024 for the commencement of the study in 2025, and participating schools have been finalized. Data collection began in August, 2025, with the analysis scheduled for October 2025. Results are expected to be published in early 2026.

## Discussion

### Anticipated Findings

This study will be one of the first TPSR-based intervention studies conducted in NSW independent and government schools to evaluate outcomes in PE settings. Its evaluation aligns with the social outcomes articulated in the rationale and aims of the NSW PDHPE K-10 syllabus. The findings will contribute valuable data for future research, enabling comparisons of social interventions, both within Australian contexts and internationally, among similar cohorts. By extending existing research that focuses on psychomotor outcomes, this study aims to explore the broader impact of social interventions in PE, particularly in relation to responsibility, leadership, motivation, and engagement. If effective, the intervention has the potential to enhance students’ social development; relationships; and, by extension, academic performance. These improvements may also help address common barriers to participation in PE, including low self-esteem, bullying, and disengagement.

### Strengths and Limitations

One of the strengths of this study is that it represents the first TPSR investigation in secondary school settings in NSW, which may prompt further research into social outcomes in Australian schools. This is a significant strength due to the aforementioned benefits of fostering positive social behaviors. Furthermore, as one of the criticisms of past TPSR studies has been the lack of methodological diversity, this study will incorporate both qualitative and quantitative methods, thereby strengthening the literature in this field and addressing known limitations. In addition, positive findings may drastically transform school and classroom culture in the participating schools, potentially increasing participation and engagement in PE, an area that has faced criticism for low student involvement previously.

Predicted limitations of the study include the focus of the intervention solely on PE classes, which may limit the transfer of outcomes to other learning contexts. Moving forward, the TPSR framework may evolve to target the overall student experience across all key learning areas; however, given its current application only in PE, the effect of such transfer is difficult to gauge.

## Appendix

Multimedia Appendix 1 SPIRIT (Standard Protocol Items: Recommendations for Interventional Trials) guidelines.

## Abbreviations

AC: HPE: Australian Curriculum: Health and Physical Education
NSW: New South Wales
PACES-PE: Physical Activity Enjoyment Scale–Physical Education version
PDHPE: personal development, health, and physical education
PE: physical education
PSRQ: Personal and Social Responsibility Questionnaire
SES: socioeconomic status
SPIRIT: Standard Protocol Items: Recommendations for Interventional Trials
TARE: Tool for Assessing Responsibility-Based Education
TPSR: teaching personal and social responsibility
